#### Calculation of sample size

From a recent trial evaluating SDM strategies for patients with dementia (EmMa project) [9], the MacCAT-T subscale scores of the 30 patients with Alzheimer’s disease (14 in the intervention, 16 in the control group) were used to define the relevant standardised location effect for the sample size calculation. While the SDM strategies in EmMa project only increased scores on the “understanding” subscale of the MacCAT-T, we expect that in our trial, the support of the familiar environment of the patient’s home will rather influence the “reasoning” subscale. Thus, we anticipate that as a result of the DECIDE intervention, the change in the reasoning score will be similar to the standardised effect of 0.582 found for understanding in EmMa project.

Due to memory limitations in the study population, we do not expect any substantial carryover effect. The relevant quantity for the sample size calculation will therefore be the location contrast estimated from both periods. However, although unlikely to be detected in a cross-over design powered for the main effect of the place the decision is made, slight differential carryover will still bias the effect. Hence, the sample size should allow us to compensate for power loss due to undetected differential carryover of up to 20% of the spatial intervention effect.

Use of a cross-over design further means that only intra-individual variance must be taken into account. The stronger the correlation between a patient’s two observations, the smaller the intra-individual variance and the smaller the necessary sample size. Although we expect some positive correlation, we will assume uncorrelated observations to be on the safe side.

Based on these assumptions, and with a two-sided significance level of α = 5%, the power.t.test () function of the R stats package (version 4.0.2) results in a total sample size of 80 patients, 160 observations, for a power of 90%. If recruitment difficulties arise, 80% power will still be achieved with 60 patients and 120 observations. If – as is to be expected – a positive correlation exists between the same patient’s measurements, even fewer patients will suffice to reach 80% power. For example, assuming a within-patient correlation of 0.2, the inclusion of 48 patients and 96 measurements will mean the power is still 80%. If a significant proportion of patients can only be studied once, the analysis could be restricted to the first observations. However, if 80 first measurements are available, the power for detecting the location effect will be reduced to 58%. In this case, we would try to include a further 16 patients and thus achieve 80% power.

Since a two-step evaluation procedure based on a linear mixed model will be used to analyse the primary endpoint, we verified the sample size in a simulation of the procedure with 10,000 analysis runs per scenario. Based on the relevant standardised effect (see above) and the variance in the ‘reasoning’ scores observed in EmMa project [9], we considered four scenarios covering a range of realistic outcomes. They are presented in Fig. 2. The simulation confirms the sample sizes obtained from the t-test formula.

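### The two first-period fallback power figures contradict each other: if 80 first measurements give 58%, then 96 give 66%, not 80%; at the stated effect of 0.582, 80 give 73%

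*Protocol article*

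**What the plan says.** All the figures are in the protocol article, under Calculation of sample size.

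- **Effect:** the expected change in reasoning is taken to be "similar to the standardised effect of 0.582 found for understanding in EmMa project".
- **Test:** power comes from R's two-sample t-test function "with a two-sided significance level of α = 5" per cent.
- **Main design:** 80 patients with 160 observations for 90% power. This allows for undetected carryover of up to 20% of the effect and assumes that a patient's two measurements are uncorrelated.
- **Fallback with one measurement per patient:** "if 80 first measurements are available, the power for detecting the location effect will be reduced to 58" per cent. The next sentence adds: "In this case, we would try to include a further 16 patients and thus achieve 80% power".

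The section on missing data refers to this fallback when too many patients complete only the first interview. The section on statistical analysis also makes the first period the main analysis if the place-by-period interaction is significant.

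**The concern.** Going from 80 to 96 patients enlarges the sample by 20%, so the noncentrality of the test grows by only √1.2 = 1.095. That is too little to lift power from 58% to 80%. The two figures stand in adjacent sentences and describe the same comparison, so at least one of them is wrong.

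They are also the figures on which the sponsor would decide whether to extend recruitment. If 58% were right, the planned extension would stop at about 66% power while the protocol claims 80%. If 58% is wrong, the protocol understates what the fallback can deliver with 80 patients.

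**Working it through.** **Inputs.** Standardised effect d = 0.582, two-sided α = 0.05 and the two-sample t-test come from the sample size section. The procedure section gives two visit orders in blocks of 4, so allocation is 1:1. Eighty first measurements are then n = 40 per place, and 96 are n = 48 per place.

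**Formula** (the one behind power.t.test):

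power = 1 − F(t₀.₉₇₅,₂ₙ₋₂ ; df = 2n − 2, ncp = d·√(n/2)), where F is the noncentral t distribution function.

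**Step 1: reproduce the protocol's crossover figures.** Differential carryover of 20% of the effect biases the AB/BA contrast by half of that, so d = 0.9 × 0.582 = 0.524. With uncorrelated observations, n is the number of observations per place. With within-patient correlation 0.2, d becomes 0.524/√0.8 = 0.586.

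| Patients | Correlation | Stated power | Recomputed |
|---|---|---|---|
| 80 | 0 | 90% | 90.9% |
| 60 | 0 | 80% | 81.2% |
| 48 | 0.2 | 80% | 81.1% |

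The method is therefore understood, and these figures stand.

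**Step 2: test the two fallback figures against each other, without assuming an effect.**

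- Solving power = 58% at n = 40 gives d = 0.489. At n = 48 that effect gives 66.0%. Reaching 80% takes 66.5, so 67, per group: 134 patients, and 134 − 80 = 54 extra.
- If 58% is a rounded value between 57.5% and 58.5%, power at 96 patients lies between 65.5% and 66.5%.
- In reverse, 80% at n = 48 implies d = 0.578, which gives 72.3% at n = 40.

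A check by hand with the normal approximation: 58% power corresponds to 1.960 + 0.202 = 2.162. Multiplied by 1.095 this is 2.368, and 2.368 − 1.960 = 0.408, which is 65.8% power. For 80% one needs 1.960 + 0.842 = 2.802, so 80 × (2.802/2.162)² ≈ 134 patients.

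**Step 3: compare with the stated effect.** The first period precedes any carryover, so the unreduced 0.582 applies.

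- n = 40: ncp = 0.582 × √20 = 2.603, power 72.9% (simulation of 20,000 runs: 73.4%).
- n = 48: ncp = 0.582 × √24 = 2.851, power 80.6% (simulation: 80.4%).

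The 80% at 96 patients reproduces. The 58% at 80 patients does not: 72.9 − 58 ≈ 15 percentage points.

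**Step 4: look for another origin of the 58%.**

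| Assumption | 80 patients | 96 patients |
|---|---|---|
| d = 0.524 (carryover allowance kept) | 63.8% | 71.9% |
| d = 0.466 (full 20% reduction) | 53.9% | 61.7% |
| d = 0.566 (small-sample correction of 0.582) | 70.6% | 78.4% |
| d = 0.582, Wilcoxon-Mann-Whitney test | 71% | 78% |
| d = 0.582, one-sided 5% | 82.5% | 88.2% |
| d = 0.582, two-sided 2.5% | 62.5% | 71.6% |
| d = 0.582, two-sided 2% | 59.1% | 68.6% |

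Reading the 16 as 16 per group (112 patients) does not help either: d = 0.489 then gives 72.8%. Unequal groups lower the power at d = 0.582 only to 60.5% even at 20 versus 60, and the planned allocation is equal. No variant tried gives 58% at 80 patients together with 80% at the enlarged sample.

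**The case against.** The strongest reply accepts the contradiction and disputes its weight. The sentence describes a contingency. The main sample size, the 60-patient figure, the endpoint and the model are untouched. If 58% is the wrong figure, as seems likely, the planned action of adding 16 patients is right, and the error merely understates power, which is the cautious direction. All of that stands. It means the 66% outcome is a risk only if the 58% is the correct figure.

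A second point is that the protocol does not say which effect it used for the fallback. The sentence follows a list of assumptions that includes the carryover allowance. If the reduced effect of 0.524 was meant, power is 64% at 80 patients and 72% at 96, so both stated figures are wrong and the top-up falls short. The misprint could also be in the count: at d = 0.582, 58% power corresponds to about 58 first measurements. So the 73% depends on 0.582 being the intended effect. There are good grounds for that, because first-period data carry no carryover and the 96-patient figure reproduces at that value, but it remains an inference.

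Neither point removes the contradiction, which holds whatever the effect. Nor does the protocol's simulation offer another basis, since it is said to confirm the sample sizes from the t-test formula.

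**Conclusion.** The concern holds. Under a two-sample t-test at two-sided 5% with equal groups, 58% at 80 patients and 80% at 96 cannot both be true, whatever the effect size.

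Which figure is wrong depends on the effect intended for the fallback. With the stated 0.582 it is the 58%, which should be about 73%, and the 16-patient top-up is sound. If the 58% is kept, the top-up reaches about 66% and roughly 134 patients are needed for 80%. The error is confined to the fallback, but it stands behind a decision on extending recruitment and is wrong as written.

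**What to change.** In the sample size section, replace 58% by 73% and state the basis: two-sample t-test, two-sided 5%, standardised effect 0.582, 40 first measurements per place, no carryover reduction. Keep 96 patients for 80% power (80.6%).

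If the 58% comes from a different effect or from the two-step simulation, state that assumption and replace the 80% claim by the power that 96 patients give under it. For the effect implied by 58% this is about 66%, with about 134 patients for 80%.

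The cost is one corrected number and a short statement of its basis. At the stated effect, no patients are needed beyond the 16 already foreseen for the fallback.

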**Fig. 2 Fig2:**
[figure not shown]
Scenarios considered in the simulation. Scenario A is the basic scenario with only a location, but no carryover or period effects. Scenarios B and C include a carryover and a period effect amounting to 20% of the location effect respectively, and in scenario D, both are included. The standard deviation of the score is 2.83 in all scenarios

### Quality control

#### Data management

The Data Management Committee (DMC) consists of a biostatistician and a data manager, neither of whom are involved in data collection. They are responsible for data digitalisation, data quality assurance and privacy protection, and for providing statistical advice and surveying the database. Further, they created the randomization list for allocating the participants to the different intervention groups. The paper-based recorded data will be digitalised in the LimeSurvey online survey tool. To monitor the data, a double data entry will be performed on one randomly selected record out of each set of ten successive records.

#### Trial monitoring

A Trial Management Committee (TMC) will be responsible for elaborating the study design and procedure, data collection and informed consent materials where appropriate. It will meet twice a week to discuss and solve current problems and initiate any necessary steps. The TMC will include the Steering Committee (SC), which organises and moderates TMC meetings, reviews the study’s progress and agrees on changes to the study protocol that become necessary during the course of the study. The SC will keep the study protocol updated and communicate all changes to the study members and the ethics committee.

#### Principal and lead investigators

The principal investigator designed the study and acquired the grant. Being the head of the SC, she is responsible for all final decisions during study implementation. She will be responsible for most of the communication with the associated partners. She declares to have no competing interests.

Lead investigators are the study physicians and neuropsychologists at each of the study centres. As part of the TMC, they represent the link between research and practice and are responsible for data collection.

#### Audits

Members of the Institute for Medical Ethics and History of Medicine at the Ruhr-University Bochum, Germany, form an independent ethics advisory board for the study. They will advise us on questions related to research ethics.

We plan to organise biannual expert workshops to obtain scientific advice from international experts from different disciplines. The topics will relate to challenging issues during the research process, e.g., clinical diagnostics of dementia, decision-making, task complexity, capacity to consent. Additionally, our cooperation partner, the Frankfurt Forum of Interdisciplinary Ageing Research, will provide theoretical input on relevant gerontological issues such as person-environment processes in aging.

Finally, we have established a patient advisory board in cooperation with the Alzheimer Society Siegen at our department. Its function is to advise researchers on practical and ethical questions that arise during the research process. We can thus adapt our research to the needs of PwAD. The patient advisory board currently consists of four patients and meets monthly. In the DECIDE project’s study presented here, we will ask the advisory board for advice on ethical questions and questions related to the study procedure or materials.

### Ethics and dissemination

The study procedure and materials have been reviewed and approved by the Ethics Committee of the Medical Council Westfalen-Lippe, the medical faculty of University of Münster (trial no. 2022–080-f-S) and the Ethics Committee of the Medical Faculty at Goethe University Frankfurt am Main (trial no. 2022–853). The study has been registered with the Germany Registry for Clinical Trials (DRKS, Deutsches Register Klinischer Studien, no. DRKS00030799). All items of the WHO Trial Registration Data Set can be found in Additional file 1. Any relevant amendments to this protocol will be communicated formally to the study registry, and to the ethics committees for approval.

#### Possible harm, ancillary, and post-trial care

In addition to routine clinical procedures at the memory clinic, participants will have two study appointments. At the beginning of each appointment, their capacity to consent to an advance directive will be assessed using standardised methods during a meeting lasting around 20 min. As the complexity of this decision-making situation is expected to be stressful for the PwAD, we will use the support strategies to minimise it. Afterwards, the PwAD can decide whether to create an advance care plan or not. The creation process will be spread over two appointments to avoid overload. Since the ACP is not part of the study, it can be tailored to the individual needs of each participant.

#### Informed consent and assent

At their final appointment at the memory clinic, the study physician will tell the participants about the study and answer any questions they have. If participants agree to participate, he will obtain their written informed consent. The information provided to participants and the informed consent form are available on request.

Since participants have a suspected or final diagnosis of dementia in Alzheimer’s disease, their capacity to consent to study participation may be an issue. Following German AWMF S2k guidelines to medical procedures, we will support the participants as far as possible. If their capacity to consent is questionable, consent by proxy will be an option but nonetheless require the patient’s assent. Patients that neither consent nor agree to consent by proxy will be excluded from study participation.

#### Confidentiality and access to data

At each of the three sessions (see Fig. 1), study documents will be filled out on paper without personal identifying information of participants. After each visit, paper documents will be scanned into the digital patient file and the originals will be destroyed. This procedure allows us to merge the three sets of anonymized documents. After completion, the relevant documents will be printed as anonymized records and safely stored in the respective memory clinic. After successful data entry and quality control, the printouts will be destroyed.

The DMC has access to all digitalised study data. Researchers graduating based on work on the DECIDE project will only have access to the data they require for their theses. The (anonymous) data used in publications will be accessible to other researchers via PsychData, a German data-sharing platform for psychological research (www.psychdata.de). Study protocols and codebooks will also be shared. After publication, the data will be made available to other researchers for six months to ten years if they have specific and reasonable requests for data usage and sign the data usage agreement.

#### Dissemination of results

It is our intention to publish findings from the study in open-access journals that enforce strict quality assurance processes (i.e., peer-reviewed journals). Every listed author will have made a substantial contribution to the manuscript. We do not intend to use any professional writers. We also plan to include our findings in the updated version of the AWMF-Guideline “Einwilligung von Menschen mit Demenz in medizinische Maßnahmen” (consent to medical treatment by people with dementia), and we will present the study results at relevant national and international conferences concerning dementia and geriatrics.

## Discussion

The current study will investigate an innovative and resource-oriented approach to SDM in PwAD. Past studies have only succeeded in improving the understanding of information by compensating for people’s impairments in verbal retrieval and have been unable to achieve any clinically relevant improvement in overall capacity to consent. We will focus on the resources of PwAD in the relational domain of communication by choosing their highly familiar home as a location for the decision-making process. We hypothesise that improving the fit between person and environment will reduce complexity and thus enhance capacity to consent. In contrast to past studies, we expect the new SDM strategy to facilitate the reasoning processes that are most challenging for PwAD. If the choice of the home as a location for decision-making has the desired effect, we expect use of the support strategy to be extended to include other important and complex decisions affecting PwAD, such as decisions on medical treatments, a final will, or on whether to move to a nursing home.

## Limitations

It will be challenging to recruit a sample of PwAD of sufficient size. However, as our study physicians provide regular care in a memory clinic, we have good access to the target population and to potential participants. Nevertheless, PwAD have limited capacities and would be required to attend two further appointments in addition to the three regular appointments at the memory clinic. As has frequently been the case in the past, this may result in our recruiting less impaired people because they have more resources and thus agree more often to study participation.

Moreover, it will not be possible to blind the study physicians to the intervention effect because they are part of the research team, and a change in location is an obvious intervention. We therefore risk bias in the assessment of capacity to consent if the study physicians unconsciously give participants higher scores either at home or in the clinic. To minimise the risk of bias, our physicians will be made aware of the possibility and use a standardised instrument for the assessment of capacity to consent.

Furthermore, the standardised assessment of capacity to consent to an advance directive using the CAT-AD is known to be more conservative than a clinical assessment [35]. Grisso and Applebaum [36] conclude that the assessment of the capacity to consent should not be wholly based on the instrument, and a sum score for overall capacity to consent should not be calculated. In our study, the final decision on whether a person is able to consent will therefore be made by using cut-off criteria at a subscale level.

### Outlook

Should the intervention prove successful, one central question for future studies will be how to implement the spatial intervention in clinical practice. In daily life, physicians working in memory clinics do not have the resources to make additional appointments with their patients at home. The economic use of the SDM strategy will therefore require persons that visit PwAD at home on a regular basis to play an important role. It is conceivable that general practitioners conducting home visits, caregivers, or dementia care nurses should play a role in the process. Future research could investigate the integration of our SDM strategy into overall dementia care management (DCM). DCM is a collaborative model of care in which qualified professionals support PwAD and their caregivers in a home setting according to their individual needs [37]. These professionals could be trained in the assessment of capacity to consent and in the use of SDM to support PwAD in complex decision-making situations.

## Data Availability

Data and materials on which published results are based will be available from the corresponding author via the data sharing platform PsychData (www.psychdata.de) upon reasonable request.

## Abbreviations

PwAD: People with dementia in Alzheimer’s disease
SDM: Supported decision making
ACP: Advance care planning
DCM: Dementia Care Management
